**Methods:**

The Jabula Uzibone study collects baseline and 12-month observation checklists at 8 sites and 6 (12.5%) key informant interviews per site at 4 TG-DSD and 4 standard sites (n=48). We seek to enroll ≥600 transgender clients, 50% at TG-DSD and 50% at standard sites: 67% clients with HIV and 33% clients without HIV per site type. Participants complete interviewer-administered surveys quarterly, and blood is drawn at baseline and 12 months for HIV RNA levels among participants with HIV and tenofovir levels among participants on pre-exposure prophylaxis. A subset of 30 participants per site type will complete in-depth interviews at baseline and 12 months: 15 participants will be living with HIV and 15 participants will be HIV negative. Qualitative analyses will explore aspects of implementation; regression models will compare viral suppression and prevention-effective adherence by site type. Structural equation modeling will test for mediation by stigma and gender affirmation. Microcosting approaches will estimate the cost per service user served and per service user successfully treated at TG-DSD sites relative to standard sites, as well as the budget needed for a broader implementation of TG-DSD.

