**Prevention-effective adherence [23]**			
	Sexual behavior	“Have you had anal or vaginal sex in the past 30 days?”	—^a^
	Condom use^b^	“How often did you use condoms when you had sex?”	—
	PrEP^c^ adherence^d^	“How many days have you missed PrEP pills in the last 30 days?”	—

^a^No relevant citation.

^b^This question is only asked of participants who report sex in the past 30 days.

^c^PrEP: pre-exposure prophylaxis.

^d^This question is only asked of participants who self-report taking pre-exposure prophylaxis.

At the baseline and 12-month visits, all participants have blood drawn by a professional nurse for laboratory analysis. Serums from participants on ART are tested for HIV RNA. HIV RNA levels <50 copies/mL are the threshold for viral suppression, consistent with South African national guidelines [79]. Dried blood spots from participants on PrEP will be tested for tenofovir diphosphate levels [80,81]. Levels >700 fmol/punch are consistent with ≥4 doses per week and will be used as a marker for adherence [82,83].

Thirty (5%) of the 600 enrolled transgender participants who complete the quantitative survey and laboratory analyses at baseline are invited to participate in longitudinal qualitative IDIs at baseline and 12 months. IDIs are most appropriate for eliciting detailed accounts of participant experiences and perceptions of service delivery models. The open-ended nature of IDIs provide the opportunity to more deeply explore issues relevant to the study aims. Embedding qualitative data collection within implementation research can enrich the understanding of how and why service delivery models work or do not work [84,85]. Longitudinal interviews are important to study how participants experience, interpret, and respond to the service delivery model over time [86].

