	**Client**			
		IDIs with transgender participants	Tell me about your experience receiving care at the site.	
		Survey with transgender participants	Intersectional stigma scale by Scheim and Bauer [77], Psychological Gender Affirmation scale by Sevelius et al [78], and GAHT use by self-report.	
		Laboratory test with transgender participants	HIV RNA level by serum analysis (for transgender participants on ART) and tenofovir level by DBS^i^ (for transgender participants on PrEP)	

^a^GAHT: gender-affirming hormone therapy.

^b^ART: antiretroviral therapy.

^c^PrEP: pre-exposure prophylaxis.

^d^KII: key informant interview.

^e^AIM: Acceptability of Intervention Measure.

^f^IAM: Intervention Appropriateness Measure.

^g^FIM: feasibility of intervention measure.

^h^IDI: in-depth interview.

^i^DBS: dried blood spot.

Qualitative interview (KII and IDI) recordings will be transcribed and translated into English. The transcripts, field notes, and narrative summaries will be uploaded into qualitative data management software, Atlas.ti (ATLAS.ti Scientific Software Development GmbH), to facilitate analyses. During regularly scheduled meetings, the study team will review field notes, transcripts, and summaries; discuss emerging themes; and revise interviewing and coding strategies, as needed.

Statistical analysis of quantitative data will be performed using Stata (StataCorp) and MPlus (Muthén & Muthén). Data exploration of key variables will be conducted to assess for implausible values and determine whether statistical assumptions (eg, normal distributions of data) for planned statistical analyses are satisfied. Categorical variables will be reported as frequencies and percentages, with means and SDs or medians and IQRs reported for continuous variables. Patterns of missing data will be examined, including testing for differences between participants with and without missing data. A series of sensitivity analyses will be conducted to evaluate the robustness of conclusions drawn from the primary models to departures from the missing at random assumption by comparing the magnitude of the primary effect. In the rare situation that >10% missing data is observed, we will use multiple imputation, as appropriate. We will specify 2-sided tests, .05 significance level (α=.05), and compute 95% CIs throughout.

### Qualitative Data Analysis for Aim 1

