The second hypothesis is that rates of prevention-effective adherence are more likely to increase among transgender people who are HIV negative at TG-DSD sites than among those at SSD sites, over the 12-month study period. We will follow the same steps outlined above for the primary hypothesis. However, we define the outcome measure (prevention-effective adherence) as the proportion of (1) participants on PrEP with TFV levels >700 fmol/punch and (2) participants who are not on PrEP who report no condomless intercourse during the prior 30 days. The estimate will be the absolute difference in the change in the proportion who achieve prevention-effective adherence during the study period comparing those at TG-DSD versus SSD sites. In addition, we will estimate the difference between TG-DSD and SSD sites at 12 months, considering baseline values.

Clients who receive SSD services on enrollment may switch to TG-DSD over time, thereby reducing the sample size of the SSD arm and creating a threat to internal validity. To identify and account for switches over time, we will update information about where the participant is receiving care at every study visit. Participants who transfer from an SSD site to a TG-DSD site will be censored after the date of their last visit for the primary analysis. It would be inappropriate and unethical to require participants to continue receiving care at a specific site, therefore we will use careful tracking to inform an exploratory dose-response analysis that considers the amount of time a participant received care at the TG-DSD sites. The amount of time receiving care at the TG-DSD site will be the independent variable, with the change in outcome from baseline to 12 months as the dependent variable.

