### Statistical Power

Power analyses and sample size calculations were based on the primary outcome of viral suppression (aim 2). No viral load data are available for transgender people in South Africa disaggregated from other key populations. The only South African data that includes transgender women and uses the current nationally recommended threshold for viral suppression includes cisgender men who have sex with men. Nonetheless, the study found a viral suppression rate of 47% [101]. One study of transgender people receiving TG-DSD in South Africa found that those on GAHT were 3 times more likely to be virally suppressed compared to transgender people who are not on GAHT [49]. This suggests an effect size of at least 20%. We consider an effect size as low as 15% to be clinically significant.

On the basis of the aforementioned data and clinical experience, we anticipate that current viral suppression rates will be approximately 65% at baseline, rising to 85% at 12 months among TG-DSD participants, and approximately 61% at baseline, rising to 66% at 12 months among SSD participants. This 20% difference from baseline to 12 months for TG-DSD participants and 5% difference from baseline to 12 months for SSD participants represents a difference in the absolute change in viral suppression rates of 15%. Using *r*=1, α=.05, power of 1− β=.80, and p_1_=viral suppression in the SSD and p_2_=viral suppression in the TG-DSD group and difference of p_2_ – p_1_=.15, the minimum sample per group will be 172 for both TG-DSD and SSD, for a total minimum sample size of 344. Adjusting for loss to follow-up of approximately 12%, a sample of ≥200 in each group, for a total of ≥400 transgender people on ART, provides adequate statistical power for planned analyses.

Loss to follow-up is a challenge for any longitudinal study. We will make every effort to minimize loss to follow-up by collecting multiple forms of contact, reaching out monthly to update contacts, collecting data in the field as well as the study site, and providing remuneration for study participation. We are enrolling a larger sample size than required by the power calculations to allow for potential loss to follow-up without loss of statistical power.

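### Censoring SSD clients who transfer to TG-DSD removes their only follow-up outcome from the primary analysis, in one group and one direction, with no correction planned

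*Protocol article*

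**What the plan says.** All places are in the protocol article.

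- **Switching.** Data Analysis for Aim 2 expects some SSD clients to move to TG-DSD, "thereby reducing the sample size of the SSD arm and creating a threat to internal validity". Care site is updated at every study visit. The rule for the primary analysis is: "Participants who transfer from an SSD site to a TG-DSD site will be censored after the date of their last visit". Time spent at TG-DSD then enters only an "exploratory dose-response analysis that considers the amount of time a participant received care at the TG-DSD sites", whose dependent variable is the change in outcome from baseline to month 12.
- **Outcome timing.** Overall Study Design and the client-level data collection section place HIV RNA at baseline and month 12 only. The quarterly visits between are surveys.
- **Model.** The primary estimate is a difference-in-differences (D-i-D) from a mixed-effects binomial model with random intercepts for site. No client-level random effect is named.
- **Safeguards.** Inverse probability of treatment weighting is held in reserve for differences between the groups (Exploratory Analyses). Missing-data sensitivity analyses are planned, and: "In the rare situation that >10% missing data is observed, we will use multiple imputation, as appropriate".
- **Who is tested.** The laboratory paragraph says "Serums from participants on ART are tested for HIV RNA". The abstract says "blood is drawn at baseline and 12 months for HIV RNA levels among participants with HIV", and Table 1 lists HIV RNA for all participants living with HIV.

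**The concern.** With two outcome times, censoring a client before month 12 does not shorten follow-up; it deletes the whole follow-up outcome. The baseline value remains. The SSD change is then a month-12 proportion among stayers minus a baseline proportion among everyone. TG-DSD has no matching exclusion, so the selection does not cancel in the D-i-D.

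Transfer is a choice made after baseline and may be related to outcome. The article gives no reasons for transfer, but it makes a link plausible: hormone therapy is not available at public primary care facilities, and Statistical Power cites a study in which TG-DSD clients on hormone therapy were three times more likely to be suppressed. Transfer is also practical, since each SSD site lies in a TG-DSD catchment area and two TG-DSD sites stand on an SSD campus.

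The same analysis steps serve hypothesis 2, and Aim 3 builds cost per successful outcome on month-12 results, so the problem is not confined to one estimate.

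**Working it through.** **The plan's own figure.** Statistical Power gives 172 per group, raised to at least 200 ("Adjusting for loss to follow-up of approximately 12" per cent). The usual two-proportion formula (pooled variance, two-sided alpha 0.05, power 0.80, equal groups, no continuity correction) returns exactly 172 for 47% against 62%. The 47% is inferred from the cited external rate; the article does not state p1. Then 172 / 0.88 = 195.5, so 196, consistent with 200.

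**Sample left in SSD.** After 12% loss, 200 × 0.88 = 176, which is 4 above 172. The share that may switch before SSD falls below 172 is 1 − 172/176 = 2.3%. No switching rate is given, so the following rates are assumed:

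| Switching | SSD analysable | Power, 176 in TG-DSD, 47% vs 62% |
|---|---|---|
| 0% | 176 | 0.81 |
| 5% | 176 × 0.95 = 167 | 0.80 |
| 10% | 176 × 0.90 = 158 | 0.79 |
| 20% | 176 × 0.80 = 141 | 0.76 |

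The loss of power is modest. Bias matters more.

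**Bias from censoring.** Planning rates: TG-DSD 65% to 85%, SSD 61% to 66%, so the true D-i-D is 20 − 5 = 15 points. Let s be the share of SSD censored and q the month-12 suppression those clients would have had by staying in SSD (both assumed).

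SSD rate among stayers = (0.66 − s·q) / (1 − s)

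Observed D-i-D = 0.20 − (stayer rate − 0.61)

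| s | q | Stayer rate | Observed D-i-D |
|---|---|---|---|
| 10% | 46% | 68.2% | 12.8 points |
| 10% | 66% | 66.0% | 15.0 points |
| 10% | 86% | 63.8% | 17.2 points |
| 20% | 46% | 71.0% | 10.0 points |
| 20% | 66% | 66.0% | 15.0 points |
| 20% | 86% | 61.0% | 20.0 points |

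**Dilution if switchers are kept as enrolled.** If they reach 85% rather than 66%, SSD month 12 rises by s × (0.85 − 0.66): 1.9 points at 10% and 3.8 points at 20%. The D-i-D reads 13.1 or 11.2 points.

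**Secondary: narrower reading of the on-ART wording.** Suppose people off ART at month 12 are untested, and all unsuppressed. The rate among those on ART = overall rate / (1 − share off ART). For 15% off ART in SSD and 5% in TG-DSD: (0.85/0.95 − 0.65) − (0.66/0.85 − 0.61) = 0.245 − 0.166 = 7.8 points. The same formula gives 12.1 at 10%/5%, 16.0 at 5%/5%, 17.1 at 10%/10% and 18.4 at 15%/15%. All stopping rates are assumed.

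**The case against.** **Censoring is a choice of estimand.** Censoring at crossover aims at the effect of receiving each model, and the article is open about the threat. Analysis by enrolment group answers a different question, and its dilution (1.9 to 3.8 points above) is similar in size to the possible bias. This stands as a reason to report both. It does not rescue the rule as written: even for the effect of staying on each model, unweighted censoring is unbiased only if switchers would have done as well in SSD as SSD clients overall.

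**Other safeguards exist.** The missing-data sensitivity analyses could be extended to switchers, but nothing says they are. The planned weighting concerns group differences, not censoring.

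**The wording leaves room.** The last visit is not defined. If it meant the last study visit, month 12 might survive. The word censored and the stated reduction of the SSD sample favour the other reading. Silence on moves out of TG-DSD may be filled in a fuller plan; as printed, the rule runs one way.

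**Stronger readings that the article does not support.** A reader might infer that people who stop ART go untested. But on ART also serves as the name of the enrolment stratum (the recruitment paragraph and Statistical Power), the abstract and Table 1 go by HIV status, and blood is drawn from everyone at month 12. Nor does the article show that the narrower reading would shrink the effect; the direction reverses when stopping is equal in both groups. A reader might also infer that dissatisfaction drives switching, but no reasons are documented. Calling more than 10% missing rare sits awkwardly with a planned 12% loss, but that loss would itself trigger imputation, so the point is minor.

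**Conclusion.** The point stands for the primary estimate. As written, the rule removes the only follow-up outcome of SSD clients who transfer, keeps their baseline value, and applies to one group and one direction with no correction. The size cannot be fixed from the article: shifts of up to 2.2 points at 10% switching and 5.0 points at 20%, either way, against a planned 15. These rest on the assumed switching shares, on counterfactual suppression of 46% to 86%, and on reading the last visit as falling before month 12. More than about 2% switching takes SSD below the stated 172, but the power cost is small. The on-ART wording is an inconsistency to reconcile, not an established exclusion; under the assumed stopping rates the narrower reading would give about 8 to 18 points.

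**What to change.** 1. **Primary analysis.** Classify participants by site type at enrolment and use every month-12 result, whatever the switching in either direction.
2. **Sensitivity analysis.** Keep the censored analysis, apply it to moves in both directions, define the last visit, and use inverse-probability-of-censoring weights built from the quarterly data. Report it beside the primary result, with the number of switchers in each direction.
3. **Denominator.** State that month-12 HIV RNA testing and the primary denominator cover everyone enrolled in the HIV stratum, whatever their ART status at month 12, and align the abstract, Table 1 and the methods.
4. **Minor.** Describe multiple imputation as expected, given the planned 12% loss.

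The cost is mostly wording. Care site is already tracked at each visit, the dose-response analysis already needs switchers' 12-month change, and blood is already drawn from all participants, so at most a few extra HIV RNA assays are needed. The price is dilution of the as-enrolled estimate towards the null if switching is common, which is why both analyses should be reported.

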An experienced qualitative researcher conducts the KIIs after the informed consent process. A semistructured KII guide will be used to organize the interview. KIIs last approximately 60 minutes and include open-ended questions that explore facilitators, barriers, strengths, and weaknesses of the DSD and SSD approaches and recommendations for improving service delivery. At the end of the qualitative interview, participants complete a brief, interviewer-administered quantitative tool measuring antitransgender stigma [71] and validated measures of intervention acceptability, feasibility, and appropriateness [72,73]. KIIs are audio-recorded with permission of the participant, and notes are taken during and after the interview to facilitate accuracy and appropriate analysis. Where possible, interviewers are fluent in local languages. When interpretation is required, a trained study staff member interprets during the interview.

We collect data on the costs of implementation at all TG-DSD sites by conducting a bottom-up analysis of the resources used and costs accrued by all transgender cohort participants who receive TG-DSD. We also collect facility-level data on overhead cost items, such as space, administration, and utility costs, and allocate these to the service and our cohort based on the number of visits. We use our extensive database of public sector prices and salaries, as well as information on staff levels at each site, to estimate the public sector costs; these are data we have used in other costing studies in South Africa [53,74,75].

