#### Client-Level Eligibility, Recruitment, and Data Collection

Participants complete study data collection visits with the study team in a dedicated room at the site or in the community. Over the 12-month study period, participants complete 5 study visits: baseline, 3, 6, 9, and 12 months. At each visit, trained study staff use electronic tablets to administer quantitative surveys lasting 30 minutes. Surveys assess the key measures listed in Table 3. Survey data are collected and managed using REDCap (Research Electronic Data Capture; Vanderbilt University), which synchronizes with the encrypted cloud-based server at Wits RHI, where it is stored for analysis.

**Table 3 table3:** Key quantitative survey measures.

Construct		Measure	Citation

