Descriptive statistics will be used to characterize each measure overall and by site. On the basis of a score of 4 (agree) for all 4 items in the scale, a summary score ≥16 on each scale would be consistent with overall agreement that the strategy was acceptable or feasible, respectively [73]. Therefore, we will test the hypothesis that the overall mean score for each measure (AIM and FIM) is ≥16 using a 1-sample *t* test. If score data deviate from normality (skewed or nonnormal), we will conduct a 1-sample Wilcoxon signed test. We will conduct a secondary analysis to test for significant changes in baseline and 12-month scores across sites using paired sample *t* tests for normally distributed data or Wilcoxon signed rank tests if the data are nonnormal.

Using data from both study arms, facility-based stigma will be measured using the brief health facility stigma tool [71]. Each item includes 4 response options on a Likert scale that ranges from “never” to “most of the time.” Higher scores indicate greater facility-based stigma. Descriptive statistics will be generated as outlined earlier for the implementation outcome measures. We will compare mean summary scores at TG-DSD sites versus SSD sites at baseline and at 12 months, using 2-sample *t* tests if normally distributed or Wilcoxon rank tests if nonnormal. Exploratory analyses will include Pearson correlation analyses and bivariate regression to assess associations between site characteristics (eg, location and urbanicity), including facility-based stigma scores and the aforementioned implementation outcome scores.

### Qualitative and Quantitative Data Integration for Aim 1

Qualitative and quantitative data will be integrated using results-based convergent synthesis in which they will be analyzed separately then merged using joint display [96-98]. Qualitative themes will triangulate and provide context for facility stigma scores and implementation measures. Data from the checklists will be integrated into the joint display to assess visually any relationships between site features and the relationship between TG-DSD and HIV outcomes. Integrated displays will be used to identify implementation patterns. The qualitative code density (frequency of each code) will be displayed by service delivery model (TG-DSD vs SSD). Visualization will facilitate identification of similarities and differences in participant experiences across models.

### Data Analysis for Aim 2

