We will use quantitative methods to evaluate the effectiveness of TG-DSD for viral suppression and prevention-effective adherence and to assess stigma and GAHT use as potential mediators. As noted earlier, our first hypothesis is that rates of viral suppression are more likely to increase among transgender people on ART at TG-DSD sites than among transgender people on ART at SSD sites over the 12-month study period.

The primary outcome measure is the proportion of transgender people on ART with viral suppression (HIV RNA <50 copies/mL). Descriptive analyses will summarize HIV viral suppression comparing participants at TG-DSD versus SSD sites as well as by gender identity at baseline and 12 months. Percent distributions will be computed for categorical variables and means, ranges, SDs, medians, and IQRs will be presented for continuous variables stratified by attendance at TG-DSD versus SSD sites. The primary estimate for this aim is the absolute difference in the change in proportion of virally suppressed during the study period between participants at TG-DSD sites and those at SSD sites. A difference-in-difference (D-i-D) analysis will be conducted to account for anticipated differences between groups at baseline (TG-DSD vs SSD). In addition, we will compare differences at 12 months considering baseline values to enhance the robustness of the estimators of the differences in the 2 groups.

A mixed-effects binomial model will be fit, where the binary viral load suppression status of each client is regressed on fixed effects for time (baseline vs 12 months), TG-DSD versus SSD site, the time by site model interaction, and client-level covariates (age and gender identity). In addition, random intercepts for each of the sites will be included in the model to account for within-site correlation. The D-i-D estimator is the estimated regression coefficient for the time by service delivery model interaction term. All models will account for clustering and be adjusted for relevant confounders in baseline covariates.

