The third hypothesis is that stigma and gender affirmation will mediate relationships between service delivery models (TG-DSD vs SSD) and HIV outcomes (viral suppression and prevention-effective adherence). Mediation analyses will be used to investigate whether any association between service delivery models and HIV outcomes are significantly mediated by stigma (measured using Nyblade et al [71], Testa et al [76], and Scheim and Bauer [77] scales in Table 3) or gender affirmation (measured using the proportion of participants on GAHT and the Sevelius et al [78] gender affirmation scale in Table 4). Structural equation modeling will be used for this analysis. Structural equation modeling provides tests of the direct and indirect paths from the independent variable to the dependent variables [99]. The independent variable will be the service delivery model (TG-DSD vs SSD), and the dependent variables will be change from baseline to 12 months in the mediators (stigma and gender affirmation measures) and change from baseline to 12 months in the outcomes (difference in viral suppression and difference in prevention-effective adherence). Structural equation models will test direct paths (eg, from serviced delivery model to viral suppression) and indirect paths (eg, from service delivery model to stigma and from stigma to viral suppression). The basic model to be tested for this analysis is in Figure 1. We will assess standard fit statistics for the overall model: model chi-square, adjusted goodness of fit, comparative fit index, and standardized root mean square error of approximation.

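### The H3 mediation model takes mediator and outcome change over the same 12 months, so it cannot establish time order, and the protocol conflicts on who completes one of its stigma scales

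*Protocol article*

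**What the plan says.** **The model.** In Data Analysis for Aim 2, service delivery model is the independent variable. The text then names as dependent variables "change from baseline to 12 months in the mediators (stigma and gender affirmation measures) and change from baseline to 12 months in the outcomes", with the outcome part spelled out as "change from baseline to 12 months in the outcomes (difference in viral suppression and difference in prevention-effective adherence". The indirect path given as an example runs "from service delivery model to stigma and from stigma to viral suppression". For hypothesis 1 the same section treats suppression as yes/no: "the binary viral load suppression status of each client is regressed on fixed effects for time".

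**The visits.** Under Client-Level Eligibility, Recruitment, and Data Collection, "participants complete 5 study visits: baseline, 3, 6, 9, and 12 months", with a survey at each. Overall Study Design has the quarterly survey cover stigma and gender affirmation, and has viral load and tenofovir measured at baseline and month 12 only. Exploratory Analyses for Aims 1 and 2 uses the five-visit series of stigma, affirmation and hormone-therapy use to describe trends by service model. It does not link that series to HIV outcomes.

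**The stigma tool.** The mediation paragraph lists three stigma scales, one of which is the Brief Health Facility Stigma Tool (reference 71). At the end of the staff key informant interview, according to Facility-Level Eligibility, Recruitment, and Data Collection, "participants complete a brief, interviewer-administered quantitative tool measuring antitransgender stigma [71". Table 4 places the scale under staff interviews. Quantitative Data Analysis for Aim 1 says that "facility-based stigma will be measured using the brief health facility stigma tool [71" in both arms, without naming the respondent. The client-level section, however, says that client surveys assess the Table 3 measures, and Table 3 includes this tool.

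**The concern.** Mediation is a claim about sequence: service model alters stigma or affirmation, which then alters suppression or adherence. When both changes are taken from baseline to month 12, a client who became suppressed and then felt better treated contributes the same data as one who felt better treated and then became suppressed. A reverse path could therefore be reported as mediation. Hypothesis 3 is a numbered hypothesis, the Introduction promises evidence on how the model works, and Expected Findings already anticipates a mediated effect.

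A mediator score obtained only from staff would be constant across clients of a site. It would be tied to every other feature of that site and could not show that an individual client's experience carried the effect.

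**Working it through.** **1. Time order, from the text.** The plan gives no sample size or power figure for hypothesis 3, so there is no plan figure to reproduce.

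- Mediators: baseline and months 3, 6, 9 and 12.
- Outcomes: baseline and month 12.
- Planned pairing: mediator change 0 to 12 with outcome change 0 to 12.
- Pairing the data allow: mediator change 0 to 6 (or 0 to 9) with the outcome at month 12, given baseline.

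The second pairing puts the mediator measurement before the final outcome measurement. The first does not.

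**2. The change score for suppression.** Inputs are the anticipated rates in Statistical Power: TG-DSD 65% to 85%, SSD 61% to 66%. A client's difference can be only -1, 0 or +1. Let b and f be the baseline and month-12 rates and p11 the share suppressed at both times. Then P(+1) = f - p11, P(-1) = b - p11, and P(0) is the remainder. The plan does not give p11, so two cases are shown.

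| Arm | Assumption | p11 | P(+1) | P(-1) | P(0) |
|---|---|---|---|---|---|
| TG-DSD | independent times | 0.65 × 0.85 = 0.5525 | 0.2975 | 0.0975 | 0.605 |
| TG-DSD | nobody loses suppression | 0.65 | 0.20 | 0 | 0.80 |
| SSD | independent times | 0.61 × 0.66 = 0.4026 | 0.2574 | 0.2074 | 0.535 |
| SSD | nobody loses suppression | 0.61 | 0.05 | 0 | 0.95 |

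Most clients score 0, and the 61% to 65% suppressed at baseline can score only 0 or -1. The mean score is nevertheless 0.20 in TG-DSD and 0.05 in SSD, and 0.20 - 0.05 = 0.15 is the planned difference in change. The coding is coarse, but it matches the hypothesis 1 estimand.

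**3. Illustrative simulation.** 200 × 0.88 = 176 clients per arm, 1,500 runs, linear models, no clustering. Mediation is signalled when both paths have p < 0.05. All coefficients are assumed. X is the arm, M the mediator, Y the outcome, and e standard normal noise.

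- *Reverse causation only:* M6 = 0.5·M0 + 0.8e; logit P(Y12) = -0.3 + 1.2·Y0 + 1.1·X; M12 = 0.7·M6 + 1.0·(Y12 - Y0) + 0.6e. Mediation is signalled in 28.7% of runs by change-on-change and in 0.2% by the month-6 model adjusted for baseline.
- *True mediation through month 6:* M6 = 0.5·M0 + 0.4·X + 0.8e; M12 = 0.7·M6 + 0.2·X + 0.6e; logit P(Y12) = -0.1 + 1.2·Y0 + 0.5·M6 + 0.5·X. Mediation is detected in 6.5% and 87.3% of runs respectively.

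The first scenario lets the outcome act on the mediator only after month 6, so the low rate for the lagged model is largely built in. The simulation shows direction, not size.

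**4. Who completes the tool.**

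- *For staff:* the interview procedure; the staff-interview row of Table 4; its absence from the client-survey row of Table 4; and Table 3's separation of this scale (enacted stigma) from the experienced-stigma scales. Table 3 also holds the acceptability, feasibility and appropriateness measures, which other sections assign to staff, so it appears to be a pooled list.
- *For clients:* the sentence that client surveys assess the Table 3 measures, and the mediation paragraph's use of the scale.
- *Weak evidence:* absence from the Table 4 client row, since that row gives examples and also omits the Gender Minority Stress and Resilience measure.

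If staff only, there are 6 respondents at each of 8 sites, hence at most 8 site values, 4 per arm. Staff who leave are replaced by someone in the same role, so the 12-month change would not always be within person.

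**The case against.** **The change-score model is defensible.** Difference-in-differences was chosen because the arms are expected to differ at baseline. Differencing removes stable differences between clients, and section 2 of the working shows that the mean change score reproduces the hypothesis 1 estimand. A month-12 model adjusted for baseline targets another quantity and need not agree with it when baselines differ. This stands, and it is a reason to add a model rather than replace one. The link function and coding are details an article may leave to the analysis plan, and Figure 1 is not shown, so the coarse coding is not itself an error.

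**A lagged model does not settle direction.** A client could become suppressed at month 2 and report less stigma at month 6. Clients are also already in care at their site type at baseline, so earlier effects and mediator-outcome confounding remain. This also stands.

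**Stronger readings that the documents do not support.**

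- A reader might infer that the planned model cannot show mediation at all. It can estimate an indirect association consistent with mediation; what it lacks is time order.
- A reader might divide 344 completers by 8 sites and infer that precision is overstated about 43-fold. That ratio is the mean cluster size. For a site-level predictor the variance inflation is 1 + (43 - 1) × ICC, which at assumed ICCs of 0.01, 0.05 and 0.10 is 1.42, 3.1 and 5.2. Data Analysis for Aim 2 also promises that all models allow for clustering.
- A reader might take staff completion of the tool as settled. It is the better-supported reading, but the text conflicts.

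**Conclusion.** The point holds on two counts. First, the stated model uses one window for mediator and outcome and leaves the intermediate mediator data out of hypothesis 3, so the time order that mediation requires cannot be established from it. This rests on the text alone. Second, the protocol conflicts on who completes one of the three stigma scales. If only staff do, the scale offers at most 8 site values and cannot serve as a client-level mediator. The other two stigma scales, hormone-therapy use and the psychological affirmation scale are unaffected by this second count.

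The consequence is confined to how hypothesis 3 is interpreted. It is not the primary hypothesis, and the minimum of 172 per group concerns viral suppression and does not change. The amount of spurious or missed mediation cannot be stated from the documents, because it depends on path strengths they do not give.

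**What to change.** 1. Keep the change-score model and report beside it a mediation analysis using mediator change from baseline to month 6, with month 9 as sensitivity. The outcome is binary status at month 12 with a probit or logit link, adjusted for baseline outcome and baseline mediator, with the site clustering already promised.
2. Describe results from both models as indirect associations. State that outcomes are measured only at baseline and month 12 and that clients are already in care at baseline, so reverse causation is reduced but not excluded.
3. Reconcile the interview procedure, the client-survey text, Tables 3 and 4 and the mediation paragraph on who completes the health facility stigma tool. If staff only, remove it from the client-level model and show it by site in the Aim 1 joint display.

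Cost: wording and model syntax, with no new client data. Mediator change after month 6 (or 9) is not used in the added model. Its estimand differs from the difference-in-differences effect, so its direct and indirect parts will not add up to the hypothesis 1 or 2 result.
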